## Materials and methods

Trial design

This is a single-center, open-label, single-arm clinical trial. The PICO (Population, Intervention, Comparison, and Outcome) framework for this study is summarized in Table 1. To ensure comprehensive reporting, this protocol adheres to the Standard Protocol Items: Recommendations for Interventional Trials (SPIRIT) criteria [8]. We have included the finalized SPIRIT checklist in the Appendix.

**Table 1 TAB1:** PICO question SIP: symptomatic irreversible pulpitis; HFC: high-frequency current

Criteria	Description
P (Participants)	Patients with a tooth diagnosed with SIP
I (Intervention)	Application of HFC
C (Control)	Not applicable (single-arm trial)
O (Outcome)	Proportion of spontaneous pain resolved after intervention

Participant timeline

The schedule of enrollment, interventions, and assessments is summarized in Table 2.

**Table 2 TAB2:** SPIRIT figure

Timepoint	Enrolment &	Assessment 1	Assessment 2
	intervention	(Day 1, 2, 3, or 7	(Two weeks after intervention
	(Day 0)	after intervention)	range ±7 days)
Enrolment			
Eligibility screening	X	―	―
Informed consent	X	―	―
Intervention			
Intervention	X	―	―
Clinical assessment			
Inspection	X	―	X
Pain during treatment	―	―	X
Percussion	X	―	X
Adverse events	X	―	X
Questionnaire survey	―	X	―

Study setting

All clinical trial activities will take place at Nagasaki University Hospital in Nagasaki, Japan.

Sample size

As the clinical application of Root ZX3 for SIP lacks systematic evaluation, no preliminary data are available for a formal power calculation. This study is therefore designed as an exploratory, single-arm feasibility trial to obtain initial estimates of safety, effect size, and clinical variability.

A total sample size of 10 participants was selected based on feasibility requirements for early-phase device investigations, in which small cohorts (typically 10-20) were appropriate for identifying procedural concerns before larger trials. Given the absence of prior effect-size estimates for immediate postoperative pain relief with this device, a formal calculation would lack a meaningful basis. Data from these 10 cases will provide the necessary preliminary estimates to determine the power and sample size for future multicenter randomized controlled trials.

Eligibility screening

Eligibility will be confirmed by operators in accordance with the criteria listed in Table 3.

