**Table 3 TAB3:** Eligibility criteria SIP: symptomatic irreversible pulpitis; VAS: visual analog scale

Inclusion criteria	Exclusion criteria
Participants with a tooth	Participants with pacemakers or implantable cardioverter-defibrillators
diagnosed with SIP requiring pulpectomy	
Permanent teeth	
Teeth with spontaneous pain	
Teeth with a positive response to an electric pulp test	
Participants aged ≥18 years	
Participants who can complete the VAS assessment independently	
Teeth without periapical lesions	
Periodontal pocket depth of the target tooth <4 mm	
Absence of furcation lesions in the target tooth	
Alveolar bone resorption of the target tooth	
< one-third of the root length	
Participants who provide written informed consent	

Intervention

After enrollment, the following procedure will be performed by operators. Following infiltration anesthesia, the targeted tooth will be isolated with a dental dam, and an access cavity will be prepared in the SIP tooth's pulp chamber using a rotary cutting instrument. Only minimal pulp exposure will be created to allow insertion of the electrode tip. The tip electrode of Root ZX3 was then inserted into the pulp tissue, and HFC (Mode 4; 530 kHz) was applied three times. The access cavity will be sealed with a temporary restorative material (Caviton; GC Dental Industrial Corporation, Tokyo, Japan). Finally, a questionnaire assessing post-treatment pain will be provided to the patient.

If the target tooth presents with extensive caries and severe structural loss, it will be temporarily built up with composite resin to facilitate isolation and treatment; thereafter, the above intervention will be carried out. Any other usage of high-frequency electrosurgery instruments during treatment with Root ZX3 will be prohibited.

At 2 ± 1 weeks after the intervention, the pain questionnaires will be collected, and horizontal and vertical percussion was evaluated by operators. Then, pulpectomy was performed without infiltration anesthesia to assess pain during treatment. After the study, procedures are completed, participants were followed up as part of routine care, and appropriate treatment was provided as needed.

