All intervention procedures will be documented in the electronic medical record by the operators to enhance protocol adherence. Criteria for halting the intervention include a participant’s request to withdraw or modify their assigned treatment, any clinical deterioration or onset of comorbid conditions, and any situation where the research team deems continued participation unsuitable.

Primary endpoint

The primary endpoint is the relief of spontaneous pain on postoperative day 0. The primary outcome will be expressed as the proportion of participants in whom spontaneous pain has completely resolved on postoperative day 0.

Secondary endpoints

The secondary endpoints are: (1) Relief of spontaneous pain on postoperative days 1, 2, 3, and 7; (2) Improvement in occlusal pain on postoperative days 0, 1, 2, 3, and 7; (3) Pain during pulpectomy was experienced two weeks after the intervention; (4) Improvement in percussion pain two weeks after intervention.

Safety endpoints

For devices in this category, the following adverse events require particular attention: burns, convulsions, muscle contractions, tissue and mucosal injury and inflammation, hematoma, electric shock, cardiac arrest, and perforation. To date, such adverse events have not been reported with Root ZX3. All adverse events will be recorded and assessed for severity and causality.

Data collection

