Statistical design

The proportion of participants in whom spontaneous pain is resolved on postoperative days 0, 1, 2, 3, and 7 will be calculated using all enrolled cases as the denominator and the number of participants whose spontaneous pain has resolved as the numerator. The mean, standard deviation, median, minimum, maximum, and quartiles of preoperative and postoperative occlusal pain (VAS values) were calculated on days 0, 1, 2, 3, and 7, and those of percussion-induced pain (VAS values) will be calculated at 2 ± 1 weeks postoperatively. Fisher's exact test will analyze the presence or absence of occlusal pain (based on VAS values) on postoperative days 0, 1, 2, 3, and 7, as well as the presence or absence of improvement in percussion-induced pain (based on VAS values) at 2 ± 1 weeks postoperatively, compared with baseline. The proportion of participants with pain at 2 ± 1 weeks postoperatively will be calculated by using all cases as the denominator and the number of participants with pain as the numerator.

Participants who discontinue participation in the study will be excluded from the efficacy analysis. Data with missing values are not discarded and are subject to statistical analysis.

Access to data

The final dataset generated by this study will be accessible exclusively to the PI. Direct access for other research personnel is not permitted under this protocol.

Monitoring

A designated research staff member will conduct monitoring based on standard operating procedures, delivering findings to the PI within 14 days of the evaluation. Should any adverse events or unforeseen complications arise, the PI will provide medical intervention, notify the CRB, and brief the study team. Given that Root ZX3 has already received approval from the Pharmaceuticals and Medical Devices Agency, a separate data monitoring committee is not required.

Potential benefits and harms

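### The two-week pain proportion in effect counts a retained participant with no two-week value as pain-free, while the spontaneous-pain proportion counts a missing answer as a failure

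*Protocol article*

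**What the plan says.** All of this is in the Protocol article, Materials and methods.

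- **Spontaneous pain** (primary endpoint on day 0, secondary on days 1, 2, 3 and 7). Statistical design computes the proportion "using all enrolled cases as the denominator and the number of participants whose spontaneous pain has resolved as the numerator".
- **Two-week pain.** The same section computes this proportion "using all cases as the denominator and the number of participants with pain as the numerator". The sentence does not name the pain it means. The likely referent is secondary endpoint 3, listed as "Pain during pulpectomy was experienced two weeks after the intervention".
- **Discontinuation.** The next paragraph states: "Participants who discontinue participation in the study will be excluded from the efficacy analysis".
- **Missing values.** The sentence after that states: "Data with missing values are not discarded and are subject to statistical analysis". It does not say how a missing value is to be scored.
- **Size.** The Sample size section plans 10 participants on feasibility grounds.

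**The concern.** Both proportions place an observed count over the full set of cases. In such a formula, a participant without an observation goes to whichever side the numerator does not count. For spontaneous pain the numerator is the good outcome, so no answer means not resolved, which is conservative. For two-week pain the numerator is the bad outcome, so no value means no pain, which favours the device. The section thus handles the same kind of gap in opposite directions and does not say that it does so.

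A secondary efficacy result is at stake. The two-week visit supplies the only efficacy endpoints after day 7, and pulpectomy is done there without infiltration anaesthesia so that pain during treatment can be judged. The Sample size section also intends these data to inform the power and size of later randomised trials, so an understated pain rate could be carried into them.

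**Working it through.** The plan gives no expected rate, dropout rate or power for this endpoint, so there is no figure of its own to reproduce. The check compares what the stated formula returns with two alternatives.

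**Inputs**
- N = 10 (Sample size section).
- x = number observed with pain at two weeks. Not in the document; assumed 2 to 4.
- m = number kept in the analysis without a two-week value. Not in the document; assumed 0 to 3.

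**Formulas**
- As written: x / N
- Assessed only: x / (N − m)
- Missing counted as pain: (x + m) / N

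**Results for x = 3**

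| m | As written | Assessed only | Missing as pain |
|---|---|---|---|
| 0 | 3/10 = 30.0% | 3/10 = 30.0% | 3/10 = 30.0% |
| 1 | 3/10 = 30.0% | 3/9 = 33.3% | 4/10 = 40.0% |
| 2 | 3/10 = 30.0% | 3/8 = 37.5% | 5/10 = 50.0% |
| 3 | 3/10 = 30.0% | 3/7 = 42.9% | 6/10 = 60.0% |

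The as-written figure does not move however many values are missing. Its distance from the missing-as-pain figure is (x + m)/N − x/N = m/10, that is, 10 points per participant.

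**Range over x, at m = 3**
- x = 2: 20.0% as written, 2/7 = 28.6% assessed only, 5/10 = 50.0% missing as pain.
- x = 4: 40.0% as written, 4/7 = 57.1% assessed only, 7/10 = 70.0% missing as pain.

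**Precision.** The 95% Clopper-Pearson intervals at x = 3, m = 2 are 6.7% to 65.2% (3/10), 8.5% to 75.5% (3/8) and 18.7% to 81.3% (5/10). They overlap widely.

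**The same construction for the primary endpoint.** With 7 resolved and 2 without an answer (assumed), the formula gives 7/10 = 70.0%, against 7/8 = 87.5% among those who answered and 9/10 = 90.0% if missing counted as resolved. Here the literal figure is the least favourable of the three; for two-week pain it is the most favourable.

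**Effect of the exclusion sentence.** If everyone without a value has discontinued and is excluded, both endpoints use N − m and the asymmetry disappears. The spontaneous-pain denominator is then no longer every enrolled case, which contradicts its own definition. Exclusion is not neutral either. The Intervention section's halting criteria include a request to withdraw and clinical deterioration. If such participants are treated as discontinued, likely failures leave both numerator and denominator.

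**The case against.** The strongest reply is the discontinuation sentence. A reader might infer from the two-week formula that anyone not assessed is scored as pain-free. The document does not support that: those who discontinue are taken out altogether. Many of the people one would worry about, such as those who sought care elsewhere or deteriorated, may fall under that exclusion. Someone whose pulpectomy had to stop because of pain is not missing at all, since operators assess pain during the procedure and that is an observed pain event. This part of the reply stands and narrows the point to participants who stay in the study but lack a two-week value, for instance because the visit fell outside the 2 ± 1 week window.

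It can also be said that no scoring rule is stated and that such detail belongs in a full protocol or analysis plan that is not shown. It is correct that no rule is stated; the scoring is a consequence of the formula. But the article itself fixes the numerator and denominator and retains missing data, so the consequence follows from what is written, not from an omission.

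Finally, this is one of four secondary endpoints, no test or decision rule is attached to this proportion, and the intervals at N = 10 are wide. That stands, and it limits the weight of the point. Wide intervals do not remove a shift that always runs the same way.

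**Conclusion.** The point holds in limited form. As written, a participant retained in the analysis without a two-week pain value lowers the reported pain proportion as if pain-free, whereas a missing spontaneous-pain answer counts as a failure. At N = 10, each such participant adds 10 points to the gap between the literal and missing-as-pain figures; if nobody is missing there is no difference. The sentence excluding participants who discontinue also conflicts with the all-enrolled denominator, so the text does not settle which analysis set applies.

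The sizes rest on assumed counts of pain and missing values. The link from the two-week sentence to pain during pulpectomy is probable, not stated. Two stronger readings should be resisted. That participants with missing values are likelier to have pain is plausible but not documented. Nor does the document present this result as its principal evidence of lasting effect: it is a secondary endpoint in a study whose Conclusions put the focus on immediate performance. The change is worth making, but it does not threaten the primary analysis as defined over all enrolled cases.

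**What to change.** 1. State one analysis set, all enrolled participants, for every proportion, and reconcile the discontinuation sentence with it.
2. Report the two-week result as the number observed to be pain-free over all enrolled, so that a missing value counts as not pain-free, in line with the primary endpoint. In the example with 3 in pain and 2 unassessed, this is (10 − 3 − 2)/10 = 50%, where the current formula implies 70% without pain.
3. Show the assessed-only proportion alongside, with the number assessed (here 5/8 = 62.5% pain-free).
4. Name the two-week pain outcome that the sentence refers to.

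The cost is a few sentences in the protocol or analysis plan and no extra data collection. Recruitment is planned to run until December 2027 with no interim analysis, so the change can still be made before the results are analysed. The drawback is that the reported figure may be less favourable.

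### The day 0 primary proportion is set on all enrolled cases, yet discontinuers are excluded from efficacy, and no rule says which applies

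*Protocol article*

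**What the plan says.** All the analysis rules stand in the protocol article under Materials and methods, Statistical design.

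- **Spontaneous pain, days 0, 1, 2, 3 and 7.** The proportion "will be calculated using all enrolled cases as the denominator and the number of participants whose spontaneous pain has resolved as the numerator". Under Primary endpoint, the day 0 proportion with complete resolution is the primary outcome.
- **Pain at two weeks.** "The proportion of participants with pain at 2 ± 1 weeks postoperatively will be calculated by using all cases as the denominator". The word for enrolled is absent here.
- **Discontinuers.** "Participants who discontinue participation in the study will be excluded from the efficacy analysis".
- **Missing values.** The sentence that follows reads: "Data with missing values are not discarded and are subject to statistical analysis".

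Three other places bear on this. Under Intervention, the reasons for halting include a participant's "request to withdraw or modify their assigned treatment" and "any clinical deterioration or onset of comorbid conditions". The same section gives the order of the last visit: "At 2 ± 1 weeks after the intervention, the pain questionnaires will be collected", percussion is tested, and "Then, pulpectomy was performed without infiltration anesthesia to assess pain during treatment". Data collection places the day 0 rating after the anesthetic has worn off, typically four to six hours after the procedure.

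**The concern.** A participant who is enrolled and later discontinues belongs in the primary denominator under one sentence and is removed under another. Resolution of spontaneous pain is the main efficacy outcome, so the exclusion plainly reaches it. The article names no analysis set and gives no order of precedence.

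The exclusion works on whole participants and has no time limit. Day 0 is rated within hours of treatment, while a participant can leave at any time up to the visit at 2 ± 1 weeks, that is, up to three weeks later. Followed literally, the exclusion deletes a primary result that already exists because of something that happened afterwards.

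Leaving may be related to outcome, since a wish to withdraw and clinical deterioration are both listed as reasons for halting. The trial is open-label with one arm, and only the principal investigator has access to the final dataset. The choice between two written denominators could therefore be made with knowledge of who left and with what result. The Sample size section says these 10 cases will supply the estimates used to plan later randomized trials, so an ambiguity in the primary proportion would carry forward.

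**Working it through.** The plan offers no figure to reproduce. The 10 participants are a feasibility choice with no alpha, power or effect size. The check is to set the two rules side by side and see what each gives on the same data.

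**Inputs.** N = 10 (Sample size). The documents give no discontinuation rate and no expected resolution rate, so the counts below are assumptions.

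**Formula, day 0.** Let r be the number resolved among all 10, u the unresolved participants who discontinue, and v the resolved participants who discontinue.

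- All enrolled: r/10
- Discontinuers excluded: (r − v)/(10 − u − v)

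Intervals are exact (Clopper-Pearson) 95%.

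| Assumed data | All enrolled | Discontinuers excluded |
|---|---|---|
| r = 8, u = 1 | 8/10 = 80.0% (44.4–97.5) | 8/9 = 88.9% (51.8–99.7) |
| r = 8, u = 2 | 8/10 = 80.0% | 8/8 = 100% (63.1–100) |
| r = 8, v = 1 | 8/10 = 80.0% | 7/9 = 77.8% (40.0–97.2) |
| r = 6, u = 1 | 6/10 = 60.0% (26.2–87.8) | 6/9 = 66.7% (29.9–92.5) |
| r = 6, u = 2 | 6/10 = 60.0% | 6/8 = 75.0% (34.9–96.8) |
| r = 6, v = 1 | 6/10 = 60.0% | 5/9 = 55.6% (21.2–86.3) |

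**Direction.** With d = u + v, exclusion raises the proportion when (r − v)/(10 − d) > r/10. This reduces to v/d < r/10: leavers resolved less often than the cohort as a whole. If they resolved more often, exclusion lowers it. For a single leaver the shift is r/90 upward if unresolved and (10 − r)/90 downward if resolved. At r = 8 these are 8.9 and 2.2 percentage points. With d = 0 the two rules agree.

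**When the day 0 rating never comes back.** The questionnaires are collected only at the two-week visit, so someone who leaves earlier may have recorded a rating that the trial never receives. Suppose 7 of those who stay are resolved and the d leavers have no result. With all enrolled, and missing counted as not resolved, the result is 7/10 = 70%. Exclusion gives 7/9 = 77.8%, 7/8 = 87.5% and 7/7 = 100% for d = 1, 2 and 3. The missing-values sentence does not choose between these, because it says such data are analysed but not how they are scored.

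**Two-week pain.** This is taken here as pain during the pulpectomy. Suppose 3 of those observed have pain and d participants leave before the procedure.

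| d | All cases, leavers scored pain-free | Leavers excluded | Leavers counted as pain |
|---|---|---|---|
| 1 | 3/10 = 30% | 3/9 = 33.3% | 4/10 = 40% |
| 2 | 3/10 = 30% | 3/8 = 37.5% | 5/10 = 50% |
| 3 | 3/10 = 30% | 3/7 = 42.9% | 6/10 = 60% |

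Here exclusion gives the higher pain figure, and the all-cases denominator favours the device. The opposite arises only if someone shows pain during the pulpectomy and is then classed as a discontinuer. With one such participant and no other pain, 1/10 = 10% (0.3–44.5) becomes 0/9 = 0% (0–33.6).

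**The case against.** The best defence is that the consequence is small. Day 0 is rated within hours, so few ratings should be lost. The trial is exploratory with no success threshold, the intervals overlap widely, and CONSORT reporting is promised. With 10 participants, a reader given the counts could compute either figure. All of that stands and limits the importance of the point. It does not say which figure is the primary result, and the short interval to day 0 does not help when the exclusion also covers people who leave later.

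It could also be said that scoring detail belongs in a fuller protocol or analysis plan. Silence could be left to those documents. Here the article itself states two rules that conflict.

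Several stronger readings are tempting, and the documents do not support them.

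- **That exclusion always flatters the device.** For the primary endpoint the direction depends on the leavers' day 0 results, and dropping a resolved participant lowers the proportion.
- **That it hides pain during the unanesthetized pulpectomy.** That visit is the last study contact, after which participants pass to routine care, so little is left to discontinue. The article does not say that stopping the procedure or accepting anesthesia counts as discontinuation. The halting criteria concern the intervention, not leaving the study. For anyone who leaves before the pulpectomy, the direction is reversed.
- **That the two-week denominator conflicts just as plainly.** Its wording could mean all cases analysed. The article does not say so, but the conflict is less explicit there than for spontaneous pain.

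**Conclusion.** The conflict is real for the spontaneous-pain proportions on days 0, 1, 2, 3 and 7, and so for the primary endpoint. Nothing in the article resolves it. It should be corrected before analysis, though it does not threaten the trial.

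The size rests on assumed counts. With 8 of 10 resolved, one discontinuer moves the primary proportion from 80% to 89% or to 78%, and two unresolved discontinuers move it to 100%. The exact intervals overlap widely throughout, and without discontinuers there is no effect. For two-week pain the documents support only a weaker statement: the denominator is not clearly defined, and exclusion can move the result either way.

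**What to change.** Replace the exclusion sentence under Statistical design with:

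> All enrolled participants stay in the denominators for spontaneous pain; results collected before discontinuation are kept and analysed, and a missing result counts as not resolved. For pain during pulpectomy, observed results are kept whatever happens afterwards; the proportion is reported among participants who underwent the pulpectomy, with the number who did not and a version counting them as having pain. An analysis excluding discontinuers may be added as a sensitivity analysis.

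The sentence that sets the two-week denominator should be aligned at the same time, or a new conflict replaces the old one. Keeping everyone in that denominator without a scoring rule would not do, because those who never reach the pulpectomy would then count as pain-free.

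The cost is a few sentences, with no new visit, data item or participant. Recruitment is planned to run until December 2027, so there is time before analysis. The day 0 proportion may come out less favourable. For example, if 8 of 10 truly resolve and one of those 8 leaves without returning the questionnaire, the rule gives 7/10 = 70%, against 7/9 = 77.8% in the sensitivity analysis. Data must still be removed where a participant withdraws permission to use them.
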